#### Additional measures

● The Mini-Mental State Exam (MMSE) [42]. This short test is a commonly used screening instrument of cognitive function with scores ranging from 0 to 30. MMSE scores lower than 24 are reliably associated with the diagnosis of dementia or other organic mental disorders. Although patients with frank dementia will have been detected and excluded from the study, it is possible that, in this patient population, some subjects will have previously unrecognised mild degrees of cognitive impairment, and thus that cognition may act as a confounder.

● Charlson Comorbidity Score [43]. This is a weighted index for classifying comorbidities’ severity, validated for estimating the risk of morbidity and mortality in longitudinal studies.

● Self-reported past psychiatric history will be obtained during the pre-surgery assessment to account for previous psychological problems.

● Participants will be asked to rate their adherence to mindfulness practice at 12 months through a questionnaire that includes a Likert scale assessing individual motivation to continue mindfulness practice and questions regarding the average amount of time (minutes) spent engaging in formal and informal meditation.

### Timelines

This is a 3-year study commencing June 2012 and ending May 2015. See Table 1 and Figure 1 for time points and recruitment progress.

**Table 1 T1:** Trial study visits

**Documentation**	**Visit 1**	**Visit 2**	**Visits 3–11**	**Visit 12**	**Visit 13**	**Visit 14**
Baseline data, demographics	X					
Eligibility criteria	X					
Randomisation	X					
Baseline assessments*		X				
8-week MT program+			X			
Total joint arthroplasty				X		
3 month MT booster session+					X	
3 month assessments*					X	
12 month assessments*						X

*Assessments are given to patients at their surgical review visit but completed independently. Assessments include: WOMAC; SF-12; WHOQOL-BREF; HADS; Arthritis Self-Efficacy Scale; MAAS, Carver Brief COPE; Brief Illness Perceptions Questionnaire; MMSE (administered at baseline during the pre-admission assessment).

+Applies to Attendance for Intervention Group Only.

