## Methods

### Experimental design

A randomised controlled trial of individuals undergoing TJA for end-stage arthritis. Patients in the intervention arm will undergo mindfulness training prior to TJA. Patients in the control arm will undergo TJA only. Outcomes will be compared at 12 months after TJA. The study strategy will be registered, constructed, and presented according to the recommendations of the CONSORT statement [26].

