#### Primary outcome

Will be self-reported pain and physical function measured on the Western Ontario and McMaster Universities (WOMAC) Osteoarthritis Index [32]. The WOMAC consists of 24 items covering three subscales: pain (five items), stiffness (two items), and physical function (17 items). The pain and physical function subscales will be used, each subscale transformed to a score ranging from 0 to 100, with a higher score indicating greater pain and physical function. The WOMAC is a widely-used questionnaire specifically designed to evaluate knee and hip osteoarthritis [33,34].

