### Randomisation and masking

Following consent, block randomisation will be used to determine which participant receives the intervention according to a computer-generated random assignment sequence prepared in advance. Considerable effort will be made to avoid observer bias through separation of roles and blinding of trial staff. A research assistant independent of patient recruitment and data collection will be responsible for co-ordination of patient appointments, telephone reminders, and travel assistance. The research associate (who will be responsible for patient consent) will be blinded to group allocation. Mindfulness training will be conducted by investigators who will remain blinded to outcome data throughout the study. Upon completion of the study, a biostatistician blinded to group allocation will analyse outcome data.

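### Table 1 schedules the self-completed baseline questionnaires one visit after randomisation, so knowledge of allocation can influence them

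*Protocol article*

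**What the plan says.** - **Order of visits.** In Table 1 (Timelines), the row "Randomisation" is marked at Visit 1 and the row "Baseline assessments" at Visit 2. The MT programme occupies Visits 3 to 11. A separate row for baseline data and demographics sits at Visit 1, so the table distinguishes that collection from the questionnaire pack.
- **Content of the pack.** The table footnote states: "Assessments include: WOMAC; SF-12; WHOQOL-BREF; HADS; Arthritis Self-Efficacy Scale; MAAS, Carver Brief COPE; Brief Illness Perceptions Questionnaire; MMSE (administered at baseline during the pre-admission assessment"). The tie to the pre-admission assessment is attached to the MMSE.
- **Who scores the scales.** The same footnote says: "Assessments are given to patients at their surgical review visit but completed independently". The primary outcome is "self-reported pain and physical function measured on the Western Ontario and McMaster Universities (WOMAC) Osteoarthritis Index".
- **Trigger for randomisation.** Randomisation and masking says: "Following consent, block randomisation will be used to determine which participant receives the intervention". Completing the baseline pack is not given as a precondition.
- **Masking.** That section also says: "Considerable effort will be made to avoid observer bias through separation of roles and blinding of trial staff". It then covers the research associate, the MT investigators and the biostatistician. Participants are not mentioned.
- **Control condition.** Experimental design says: "Patients in the control arm will undergo TJA only". There is no sham or attention control.
- **Use of baseline.** Statistical analysis plans t-tests or Mann-Whitney tests for continuous variables. Adjustment for confounders is a secondary analysis, used if baseline characteristics are imbalanced by chance. The Abstract refers to linear regression without naming covariates.

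**The concern.** A baseline serves as a reference point because treatment assignment cannot have affected it. Taken after a patient may have learned the allocation, it loses that guarantee. Patients here are selected for psychological distress, and most of the pack measures mood, coping, self-efficacy, illness beliefs or self-rated symptoms. Being told that one has, or has not, been given a place on an eight-week programme could plausibly move such ratings. The blinded examiner mentioned in the Abstract offers no protection, because the patient supplies the score.

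Three uses of the baseline would be affected:

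- **Imbalance check.** A difference caused by disclosure would be read as a chance imbalance and then adjusted for.
- **Baseline-adjusted regression.** The treatment estimate would inherit part of the baseline shift.
- **Mediators.** The exploratory aim concerns change in illness perceptions, cognitive distortions and coping. The coping and illness-perception starting values come from the Visit 2 pack. The cognitive-distortion scale is not in the footnote's list, so its timing is not shown.

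Patients who withdraw on hearing their allocation would also lack baseline questionnaire scores, and that loss could differ between arms.

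**Working it through.** **1. Does anything in the article reverse the order?** Table 1 puts randomisation one visit before the pack. Randomisation and masking places it after consent, which agrees with Table 1. No section says that the pack comes first or that allocation is held back until it is complete. Under Participants, the SF-12 is taken routinely at the pre-admission clinic, before consent. So the SF-12 has a pre-randomisation value and its Visit 2 score is a repeat. No such earlier score is shown for WOMAC, WHOQOL-BREF, HADS, self-efficacy, MAAS, Brief COPE or illness perceptions.

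**2. The plan's own figure.** The article gives no figure on this point, so its planning figures set the scale: difference 10, SD 20 (reading the printed +20 as ±20), two-sided alpha 0.05, power 80%. The normal formula gives n = 2 × (1.960 + 0.842)² × 20² / 10² = 62.8, so 63 per arm. The t-test version gives 63.77, so 64, as stated. The point does not depend on this, and moving the baseline leaves the sample size unchanged.

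**3. Bias formulas.** Suppose knowledge of allocation shifts one arm's mean baseline by d points and the shift has no bearing on the 12-month score.

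- Unadjusted 12-month comparison: baseline is not used, so bias = 0.
- Baseline-adjusted regression: the estimate subtracts slope × (baseline difference), so bias = slope × d. With equal SDs at both times, slope = r, the baseline to 12-month correlation.
- Change from baseline: bias = d. The article specifies no such analysis of the primary outcome, so this is context only.

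**4. Illustration.** The values d = 2 and 5 and r = 0.3 to 0.7 are assumptions; the article gives neither. With 64 per arm and SD 20, the standard error of the adjusted estimate is 20 × √(1 − r²) × √(2/64). At r = 0.5 this is 20 × 0.866 × 0.1768 = 3.06. Type I error with no true effect is Φ(−1.96 − bias/SE) + 1 − Φ(1.96 − bias/SE).

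| d | r | Bias, adjusted (points) | Share of 10 points | Type I error, adjusted |
|---|---|---|---|---|
| 2 | 0.3 | 0.6 | 6% | 5.4% |
| 2 | 0.5 | 1.0 | 10% | 6.2% |
| 2 | 0.7 | 1.4 | 14% | 8.6% |
| 5 | 0.3 | 1.5 | 15% | 7.3% |
| 5 | 0.5 | 2.5 | 25% | 12.9% |
| 5 | 0.7 | 3.5 | 35% | 28.4% |

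**5. Direction.** If hope makes MT patients rate themselves better at baseline, or disappointment makes controls rate themselves worse, the MT arm appears to start ahead. Adjustment then subtracts slope × d from its advantage at 12 months. The likely result is an understated benefit and lost power. For a true difference of 10 at r = 0.5, power of the adjusted analysis is Φ(10/3.06 − 1.96) = 90% with no shift. It is Φ(9/3.06 − 1.96) = 84% for d = 2 and Φ(7.5/3.06 − 1.96) = 69% for d = 5.

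**The case against.** **Timing of disclosure is not stated.** The bias arises when the patient learns the arm, not when the sequence is applied. The research associate who takes consent is blinded and a separate assistant books appointments, so disclosure might come only when classes are arranged, after Visit 2. A reader might take Table 1 as proof that baselines were given in full knowledge of allocation. The article does not support that. It shows that nothing prevents it.

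**The table may be loosely drawn.** Its footnote ties the MMSE to the pre-admission assessment, and the flow diagram was not available for this review. Practice may already be sound. This stands, and is why the fix includes simply correcting the table.

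**The main comparison is safe.** Outcomes are compared at 12 months by t-test or Mann-Whitney test, with adjustment secondary and conditional. This stands. A reader might infer that the primary result is biased; on the unadjusted analysis it is not.

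**Intention to treat.** A reader might also infer that losing patients before Visit 2 breaks this principle. It does not in itself. They remain in the unadjusted comparison if followed up, and sensitivity analyses are planned when more than 5% of data are missing.

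**A pre-consent SF-12 exists.** This stands, for that scale only.

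**Conclusion.** The ordering problem is real and nothing in the text shown corrects it. As written, the baseline WOMAC and the other self-completed scales can be influenced by knowledge of allocation, and patients who withdraw between Visits 1 and 2 have no baseline questionnaire scores. The harm is confined to the imbalance check and the adjustments it triggers, any baseline-adjusted regression, and the exploratory mediator analyses.

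The article does not allow the size to be known. The range of 0.6 to 3.5 points rests wholly on the assumed shift and correlation, and the understating direction rests on the hope-or-disappointment mechanism. Because the main unadjusted comparison is untouched and disclosure at Visit 1 is inferred rather than stated, this is a should-fix.

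**What to change.** - Have the baseline questionnaires completed after consent and before allocation is generated or disclosed. Either give out the pack at Visit 1 ahead of randomisation, or move randomisation to the end of Visit 2. Correct Table 1 to match, and state when participants are told their arm.
- If this is already the practice, correct Table 1 to show it.
- The trial is open to recruitment. For patients already enrolled under the present order, record whether the pack was completed before or after disclosure, and run the baseline-adjusted analyses with and without those who completed it afterwards.

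**Cost.** A reordered table and a changed site procedure, with no extra visit, staff, measurement or sample size. The one drawback is a mixed baseline procedure within the trial, which the record of completion timing makes visible.

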**Figure 1 F1:**
[figure not shown]
Trial flow diagram–first 12 months of study.

### Sample size

The sample size calculation was based on the following parameters: i) alpha value = 0.05, 2-sided; ii) power = 80%; iii) expected rates of the primary outcome 1-year post-TJA. To determine the sample size, we reviewed the data from our SVHM joint registry from 2009 to 2010 [44]. Of 1,180 patients who underwent TJA, 40% showed moderate to severe pre-operative psychological distress according to the pre-operative SF-12 MCS score. The mean difference in functional outcome scores at 12 months post-TJA between individuals with moderate to severe pre-operative psychological distress and individuals with no or mild psychological distress was 10 (+20) points. Based on these data, the sample size required in each of the 2 groups is 64. To allow for 15% attrition, 150 patients will be recruited in total. These numbers will also give more than 80% power to detect the expected minimum clinically important difference in pain and functional outcome scores between the combined MT + TJA group and the TJA alone group.

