### Intervention

The intervention group will undergo MT prior to TJA, with a ‘booster’ session at 3 months post-surgery. The 8-week program will be conducted on-site through the Department of Psychiatry at SVHM by MBSR-qualified investigators and will be repeated every 10 weeks during the recruitment phase. The program consists of: i) a personal interview to establish rapport, undertake a brief psychiatric assessment and arrive at realistic goals; ii) weekly group-based classes in mindfulness practice, 2 ½ hours, 10–20 participants, for 8 weeks plus a 7-hour Saturday session in Week 6. MT is manualized with each class covering specific, predetermined MT exercises and topics. Yoga based exercises are adapted to be performed in either sitting or lying, to accommodate the potential mobility limitations of the study population; iii) home-based assignments to encourage regular practice of learned skills, utilising a workbook and CDs with recorded meditation instructions; iv) a post-intervention evaluation interview of personal experiences, goal attainment, and future maintenance of acquired skills; and v) a ‘booster’ day-long workshop 3 months post-surgery. The rationale for this ‘booster’ session is based on a prior randomised trial in which we found that improvements in pain and physical function after TJA plateau by 6 months. Patients with sub-optimal improvements in pain and physical function at 6 months demonstrated a significant decline in their mental well-being scores at 12 months compared to those who experienced optimal physical function, whose mental well-being scores were maintained [29].

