### Statistical analysis

Statistical analysis will be by intention to treat. Categorical variables will be analysed using χ^2^ tests (or Fisher’s Exact test for small samples) while for continuous variables we will employ (parametric) *t*-tests and (non-parametric) Mann-Whitney tests for symmetrically and asymmetrically distributed data, respectively. The significance of differences in dichotomous data will be tested using generalised estimating equations or linear mixed model. If there are chance imbalances in baseline patient characteristics hypothesised to influence the main outcomes, then statistical techniques that allow adjustment for confounding variables will be used as secondary analyses. If there are more than 5% missing data, sensitivity analyses allowing for different assumptions, such as the best or worst possible scenario, will also be reported for the main outcomes of the study.

Health economic modelling will be applied to estimate the potential cost-effectiveness of MT + TJA. Decision analysis [46] will be used to compare the downstream consequences of MT + TJA versus TJA alone. The incorporation of Markov [47] and life-tabling [48] techniques will allow for the modelling of outcomes beyond one year. The main output of interest in health economic modelling is incremental cost-effectiveness ratios in terms of net costs per unit of health gain. Net costs will comprise the costs of MT + TJA minus costs saved from the reduction in downstream health services utilization. Health gains will be measured by estimating years of life gained and quality-adjusted life years gained. Both are enabled by the collection of time-to-outcome data and the latter also by collection of QoL data. All health economic analyses will be undertaken in accordance with recommended approaches, such as 5% discounting of estimated future costs and health gains. To account for any uncertainty in the data inputs for health economic modelling, sensitivity and uncertainty analyses will be undertaken via Monte Carlo simulation [49].

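### The MT arm is taught in classes, yet the sample size and the named tests assume independent patients; if outcomes correlate within class, power falls below 80% and the standard error is too small

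*Protocol article*

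**What the plan says.** The Randomisation and masking section allocates individual patients. The Intervention section then teaches the MT arm in weekly group classes, with "10–20 participants, for 8 weeks plus a 7-hour Saturday session in Week 6", and says the course "will be repeated every 10 weeks during the recruitment phase". Under Experimental design, controls have arthroplasty only, so they have no corresponding grouping.

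The Sample size section works from "alpha value = 0.05, 2-sided", 80% power and a difference between "individuals with no or mild psychological distress was 10 (+20) points". It concludes: "Based on these data, the sample size required in each of the 2 groups is 64". It adds: "To allow for 15% attrition, 150 patients will be recruited in total". It mentions no class size, ICC or design effect.

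For continuous variables, the Statistical analysis section offers t-tests and "non-parametric) Mann-Whitney tests for symmetrically and asymmetrically distributed data, respectively"; the Abstract names linear regression. Generalised estimating equations or a mixed model appear only for dichotomous data, and class is not mentioned. The primary outcome, WOMAC pain and physical function, consists of 0–100 scores and so falls under the independence methods.

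**The concern.** Patients in one MT class share an instructor and a peer group for eight weekly sessions of 2½ hours and a 7-hour day (8 × 2.5 + 7 = 27 hours). If some classes go better than others and this still shows in WOMAC at 12 months, outcomes within a class are positively correlated. The MT mean is then less precise than 64 independent patients would make it.

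Two things are at stake. A t-test, Mann-Whitney test or regression that ignores class would give intervals that are too narrow and a false-positive rate above 5%. A test that respects class would have less than the stated power. Both errors favour optimism, and both bear on the primary comparison.

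**Working it through.** **Inputs.** Difference 10, SD 20 (reading the bracketed figure as the SD), two-sided alpha 0.05, power 80%, 64 analysed per arm, 15% attrition and 150 recruited (Sample size); one course every 10 weeks and 10–20 per class (Intervention); 20 months of recruitment (Recruitment). The ICC is not given; 0 to 0.10 is assumed. Total SD is held at 20.

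**1. The plan's own figure.** With d = 10/20 = 0.5, the exact two-sample t-test needs 63.77, so 64 per arm, with power 80.1%. The published figure therefore reproduces with a design effect of 1. After attrition, 150 × 0.85 = 127.5 against 128 needed, so there is no reserve.

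**2. Class size.** 20 months = 20 × 52/12 = 86.7 weeks, or 8.7 courses at one per 10 weeks. 150/2 = 75 MT patients over 8.7 courses is about 8.7 per class at entry. With 64 analysed, 8 classes of 8 is a fair working layout.

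**3. Design effect, MT arm only.**
- DE = 1 + (m − 1) × ICC, with m = 8.
- SE = 20 × √(DE/64 + 1/64); under independence, SE₀ = 20 × √(2/64) = 3.54.
- Power, normal approximation = Φ(10/SE − 1.96).
- Power with few classes: noncentral t, noncentrality 10/SE, Satterthwaite df = (v₁ + v₂)² / (v₁²/7 + v₂²/63), where v₁ = DE/64 and v₂ = 1/64 (8 − 1 = 7 df for classes).
- Actual type I error of the naive test = 2 × [1 − Φ(1.96 × SE₀/SE)].

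Example, ICC 0.05: DE = 1 + 7 × 0.05 = 1.35; SE = 20 × √(2.35/64) = 3.83; power = Φ(2.61 − 1.96) = 74%. The df are 20.0, which gives 70%.

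| ICC | DE | SE/SE₀ | Power, design effect alone | Power, Satterthwaite df | Naive type I error |
|---|---|---|---|---|---|
| 0 | 1.00 | 1.00 | 81% | 78% | 5.0% |
| 0.01 | 1.07 | 1.02 | 79% | 76% | 5.4% |
| 0.02 | 1.14 | 1.03 | 78% | 74% | 5.8% |
| 0.05 | 1.35 | 1.08 | 74% | 70% | 7.1% |
| 0.10 | 1.70 | 1.16 | 68% | 63% | 9.2% |

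A simulation of the t-test with 8 classes of 8 agrees with the last column to within 0.1 percentage points.

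**4. Separating the two losses.** At ICC 0 there is no clustering, yet the Satterthwaite column already shows 78%. That gap is the price of estimating the MT variance from 8 classes. At ICC 0.05 the design effect takes power from 81% to 74%, and the df rule takes it on to 70%.

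**The case against.** **The ICC is unknown and may be near zero.** WOMAC is self-reported 12 months after an operation that falls between the classes and the assessment, and a class effect may not last that long. This stands. A reader might infer that 80% power is certainly not delivered and the standard error is certainly too small; the documents do not support that. At ICC 0 there is no error in the standard error, and at 0.01 the design effect costs one to two points.

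**The type I figures need a particular null.** They assume that class effects vary around a mean of zero. If MT affects nobody, the class effects vanish and individual randomisation protects the test. This stands as a condition on the figures.

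**Calendar period does not belong here.** A reader might count it among the sources of correlation within MT classes. Controls are randomised concurrently and share it; a period effect common to both arms makes the naive test slightly conservative. Only instructor and peer effects are specific to MT.

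**Larger, fewer classes look worse, but do not fit the schedule.** Five classes of 13 would take power at ICC 0.05 to about 62% with small-sample df. That layout would require dropping nearly half of the 8–9 courses that the timetable implies.

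**The class-size figures are not a firm contradiction.** About 8–9 per class assumes even enrolment and every course running; seven courses would give 75/7 = 10.7. It is a planning approximation that needs stating clearly.

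**An analysis plan could add a class term.** It could, and that would correct the standard error. But the protocol article already fixes a sample size and names tests, both on independence, and a later model term cannot by itself restore power at 64 per arm.

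**Conclusion.** The point holds in conditional form. The design is partially nested by the protocol's own description; the 64 per group is the independence figure with nothing in hand; and the methods named for the primary outcome ignore class. Any positive within-class correlation in WOMAC pushes power below the stated figure and makes the naive interval too narrow.

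For an ICC of 0 to 0.05 with about 8 classes of 8, power is about 81% down to 74% from the design effect alone, or about 78% down to 70% with small-sample df. The naive test's type I error is about 5% to 7%. At ICC 0.10 the corresponding figures are 68%, 63% and 9%. These rest on an assumed ICC, a total SD of 20, equal class sizes and no baseline adjustment. The direction is firm for any positive ICC; the size is not.

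**What to change.** - Record class membership for every MT patient. This is easiest while courses are running, and the Trial status section says recruitment is open.
- Analyse WOMAC pain and function with a partially nested mixed model: a random class effect in the MT arm only, controls as singletons, and Satterthwaite or Kenward-Roger degrees of freedom.
- Adjust that model for baseline WOMAC, which Table 1 already collects and which may recover some power. At present the Statistical analysis section keeps adjustment for secondary analyses after chance imbalance.
- Restate power as a range over an assumed ICC of 0–0.05: about 70–78% with small-sample df, before any gain from baseline adjustment.
- State the expected class size and reconcile the 10-weekly schedule (about 8–9 per class if all courses run) with the stated 10–20.

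The cost is one recorded variable and one model term, a somewhat wider interval and a less favourable stated power. No extra patients are needed. The change makes the inference valid and the power statement honest; it does not guarantee 80%.
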